## Abstract

**Background:** People with cerebral palsy (CP) present with limitations in gait and functionality, with a great impact on participation. Physiotherapy interventions based on goal-directed training (GDT), treadmill gait training (TGT), and action observation treatment (AOT) showed to be effective for improving functionality, gait and balance in children and adolescents with CP. On the other hand, since COVID-19 lockdown, telecare has an increased role in physiotherapy interventions. The aim of this randomized controlled trial (RTC) is to analyze the effectiveness of a multimodal intervention that combines face-to-face PT sessions of GDT and TGT and online PT sessions of a family-centered education program, which includes AOT activities and is effective to improve participation, gross motor function, gait and balance in children and adolescents with CP. **Methods:** A single-blinded RCT is proposed for 48 children and adolescents with CP (6–17 years old) who will be randomly allocated into two groups: the experimental group will receive six weeks of a multimodal PT intervention with 12 face-to-face sessions (GDT and TGT) and 6 online sessions of a family-centered telecare EP, which includes AOT activities. Participants in the control group will carry on with their regular PT treatment plus the EP as the experimental group. The outcome variables of participation (CAPE); gait speed and endurance (10 mm/6 mm); gross motor function (GMFM-88-SP); and dynamic and static balance (PBS) will be collected at baseline, after group interventions and 12 weeks from baseline and will be compared following standard principles for RCTs. **Conclusions**: The implementation of a multimodal PT intervention that combines face-to-face sessions of GDT and TGT and online sessions of a family-centered EP, which includes AOT activities, may be effective to improve participation, gross motor function, gait and balance in children and adolescents with CP. Trial registration: ClinicalTrials.gov with ID: NCT04778930.

## 1. Introduction

Cerebral palsy (CP) is **a** non-progressive neurological disorder caused by damage to the developing brain during the pre, peri, or postnatal period [1,2,3]. It is the most common cause of motor disability in childhood, affecting movement, posture, and coordination. The overall birth prevalence of CP is estimated to be 1.6 per 1000 live births worldwide [4]. Despite its non-progressive nature, CP leads to chronic impairments that can evolve over time, affecting an individual’s functional independence and participation in different settings, such as family, school and community.

CP children and adolescents might have a broad spectrum of impairments in body structure and function, including muscle tone alteration, postural instability, motor coordination deficits, and impaired voluntary movement control. These impairments can significantly impact functional activities and restrict participation in essential aspects of daily life, such as family interactions, education, social activities, and community engagement [5,6,7].

Children and adolescents with CP commonly experience limitations in independent mobility, primarily due to deficits in gross motor function, gait, and balance. These mobility challenges significantly affect their ability to explore the environment, engage in play, and perform different activities of daily living. Consequently, restricted mobility and participation may lead to secondary complications, including muscle contractures, joint deformities, and reduced cardiovascular fitness, which further exacerbate functional limitations [7,8,9].

Given these challenges, physiotherapy (PT) interventions play a crucial role in managing individuals with CP by addressing impairments, enhancing functional abilities, and promoting participation in meaningful activities [10,11]. Effective PT programs should adopt a holistic and individualized approach, focusing not only on improving body structure and function but also on fostering independent mobility, participation, and overall well-being.

Recent advances in research have emphasized evidence-based PT approaches that enhance mobility, function, and participation in children and adolescents with CP. Systematic reviews [12,13,14] and international clinical practice guidelines for CP interventions [15] support the implementation of task-oriented and motor learning-based interventions. Among them, goal-directed training (GDT), also referred as task-specific training (TST), is an approach that focuses on practicing meaningful, goal-oriented tasks that directly translate into improved daily function [16,17]; treadmill gait training (TGT) is widely recognized as an effective intervention for improving gait parameters, endurance, and balance in children with CP and can enhance walking ability, step symmetry, and lower limb strength, promoting independent ambulation [18,19,20]; and research indicates that action observation therapy (AOT) can significantly improve motor function, coordination, and movement efficiency [21,22,23]. AOT is an emerging motor learning-based intervention that uses mirror neuron system to enhance motor planning and execution. In AOT, children and adolescents with CP observe goal-directed actions performed by their peers, either through video demonstrations or live models, and then attempt to replicate the movements [21,22,23]. All the previously mentioned interventions work best when they are family-centered, have regular attention, follow-up and feedback by therapists, and include education programs to empower children, adolescents and their families in the achievement of functional goals [21,22,24]. The intervention goals and activities should be established among children and adolescents with CP and their families and caregivers, supported by therapists [15].

Due to the health situation caused by COVID-19, health services had to adapt, and a new vision through telecare, also called telerehabilitation, was necessary to provide alternatives for PT interventions to children and adolescents with CP [25,26]. Telecare involves the remote delivery of PT services via digital platforms, allowing real-time therapist supervision, exercise guidance, and caregiver education. PT interventions play an important role in the maintenance of function and the follow-up of individuals, in addition to giving the opportunity for Physiotherapists to be in the natural environment of the child and adolescent [27,28].

Therefore, the aim of this randomized controlled trial (RTC) is to analyze the effectiveness of a multimodal PT intervention that combines face-to-face sessions of GDT and TGT and online sessions of a family-centered EP, which includes AOT activities, to improve participation, gross motor function, gait and balance in children and adolescents with CP.

## 2. Materials and Methods

The study protocol follows the Standard Protocol Items: Recommendations for International Trials (SPIRIT) [29].

### 2.1. Study Design

A single-blinded randomized controlled trial will be conducted according to Consolidated Standards of Reporting Trials (CONSORT) guidelines [30,31].

### 2.2. Ethics Approval and Consent to Participate

This study complies with the ethical principles of the Declaration of Helsinki [32] and the Spanish Law on Personal Data Protection and Guarantee of Digital Rights [33]. The RTC Efectividad de la Fisioterapia para la mejora de la funcionalidad de la marcha y participación en el entorno en niños y adolescentes con Parálisis Cerebral: ensayo clínico aleatorio (FIMAPACE) was approved by the Ethics Committee of Animal Experimentation and Research of the University of Alcalá with the code CEI/HU/2020/39, and it is registered in the www.clinicaltrials.gov (accessed on 7 February 2023) database under number NCT04778930. Written and informed consent will be obtained from parents or guardians, and all participants will give their assent upon entering the trial, before matching and randomization. Information sessions about this study will be held for parents/guardians and participants, where an information sheet will be provided.

Once informed, parents/guardians will read and sign the informed consent. All the information collected from each of the participants will be filed in a personal PT individual file, to which a file number will be assigned in chronological order of data collection, where data collected on paper and computer data extracted from the various tests will be entered.

### 2.3. Sample Size Calculation

The authors have not found meta-analyses nor systematic reviews about the impact of the PT interventions for improving participation. The meta-analyses and systematic reviews consulted on different interventions for improving the functionality of children and adolescents with CP include samples from 10 to 30 participants [12,16,18,34,35,36]. Study samples from the CP population are not very large due to the variety of interventions and parameters for assessing function in PT interventions. As far as the authors know, there is no consensus on the parameter or predicted change in order to better estimate a sample size. Therefore, in this study, authors opted to obtain a larger sample than most previously published studies, considering 40 participants (20 in each group) for inclusion. Considering a 20% dropout rate, a total of 48 participants should be included—24 in the experimental group (EG) and 24 in the control group (CG). At the end of this study, the statistical power will be calculated.

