### 2.5. Randomization and Blinding

A total of 48 participants will be randomly allocated in 2 groups, with 24 participants in each group. The sequence will be generated randomly by computer and the participants will be allocated to EG or CG.

Two members of the research team will perform the assessments and will be blinded to group and treatment assignments.

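### The 20% dropout allowance was added to the target instead of divided out: 48 randomised leaves about 38, not the implied 40, a minor shortfall

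*Protocol article*

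**What the plan says.** Section 2.3 (Sample Size Calculation) of the protocol article explains that no effect size was available to the authors: "there is no consensus on the parameter or predicted change in order to better estimate a sample size". The number was therefore chosen by comparison with the literature, where the cited reviews cover samples of 10 to 30: "authors opted to obtain a larger sample than most previously published studies". The target is given as "considering 40 participants (20 in each group) for inclusion".

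The next sentence applies the dropout allowance: "Considering a 20% dropout rate, a total of 48 participants should be included", split as "24 in the experimental group (EG) and 24 in the control group (CG"). Section 2.5 (Randomization and Blinding) takes the result forward as the number to be randomised: "A total of 48 participants will be randomly allocated in 2 groups, with 24 participants in each group". The abstract also gives 48.

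No planned power, alpha, effect size or standard deviation is stated. On power, section 2.3 says only: "At the end of this study, the statistical power will be calculated".

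**The concern.** Raising 40 to 48 on account of dropout has one evident purpose: that about 40 should still be in the trial after the expected losses. The target, the rate and the result are all printed, so the step can be checked, and the three figures do not agree.

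The pattern is a common slip. Twenty per cent of the target was added, although dropout is a proportion of those enrolled. The result is too small for the purpose. Because section 2.3 offers no effect size or power, 20 per group is the only quantitative size target in it. A trial that met its own dropout assumption exactly would be expected to finish below that target.

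**Working it through.** **Inputs, all from section 2.3 (48 also in section 2.5)**
- Target before the allowance: n = 40 (20 per group)
- Dropout rate: d = 0.20
- Stated number to include: N = 48 (24 per group)

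**Step 1. Reproduce the plan's figure.**
n x (1 + d) = 40 x 1.20 = 48, and 20 x 1.20 = 24 per group. Both match the article exactly. The article does not print the formula; this one returns its numbers.

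**Step 2. The allowance that keeps n after a fraction d is lost.**
N x (1 - d) = n, so N = n / (1 - d) = 40 / 0.80 = 50, or 20 / 0.80 = 25 per group.

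**Step 3. What 48 leaves at the stated rate.**
48 x 0.80 = 38.4 in total, and 24 x 0.80 = 19.2 per group: about 38, or 19 per group. The expected shortfall is 40 - 38.4 = 1.6 participants, or 0.8 per group.

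**Step 4. The dropout rate that 48 can absorb.**
1 - 40/48 = 0.167, that is 16.7%.

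**Step 5. Chance of retaining the target.**
Assumption: each participant stays independently with probability 0.80.

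| Randomised | P(at least 40 stay in total) | P(both arms keep at least 20) |
|---|---|---|
| 48 (24 + 24) | 0.358 | 0.460² = 0.211 |
| 50 (25 + 25) | 0.584 | 0.617² = 0.380 |

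The right-hand column should be read across both rows. Even the correct allowance leaves only a 38% chance that both arms keep 20, so much of the 21% reflects random variation in dropout and not the arithmetic slip.

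**Step 6. Effect on the detectable difference.**
Assumptions, none of them stated in the article: two-sided alpha 0.05, 80% power, two-sample t-test, equal groups.
- 20 per group: 0.909 SD
- 19 per group: 0.934 SD

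The change is 0.025 SD. Put the other way, power to detect 0.909 SD falls from 80% to 78%. The normal approximation, (1.96 + 0.84) x √(2/n), gives 0.89 and 0.91 SD, a shift of about the same size.

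**The case against.** **The article never says that 40 will complete.** This is correct. Both 40 and 48 are described as numbers for inclusion, and retention of 40 is implied, not stated. A reader might infer that the plan promises 40 completers; the wording does not go that far. The inference that 40 is the number to be kept still stands, because otherwise the dropout sentence has no function.

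**Nothing statistical is lost.** This largely stands. The 40 comes from no effect size, SD, alpha or power. It was chosen to be larger than most earlier samples, and about 38 completers still exceeds the 10 to 30 participants that section 2.3 cites. A reader might infer that the trial is underpowered because of this slip. The documents do not support that: there is no stated power to fall short of, and on assumed inputs the change is slight.

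**The error spreads through the article.** A reader might infer this because 48 recurs in the abstract and section 2.5. It does not. Those places give only the number to be randomised and say nothing about how many will remain. They are consistent with section 2.3 and need no correction if 48 is kept.

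**Completers are not the only participants analysed.** Section 2.9 plans both intention-to-treat and per-protocol analyses, and repeated measures models over the assessments. Participants lost after the intermediate assessment may therefore still contribute. This softens the practical effect, but the disagreement between 40, 20% and 48 remains whichever analysis set is used.

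**The article condenses a fuller protocol.** That would excuse an omission. Here all three figures are printed and they conflict.

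**Conclusion.** The dropout allowance in section 2.3 is wrong as written. The plan's own figures give 50 for 40 retained at 20% dropout, and 48 leaves about 38 (19 per group). This part is arithmetic and rests on one reading only, that 40 is the number intended to remain.

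The consequence is minor: less than one participant per group in expectation. If dropouts are independent at 20%, the chance of retaining at least 40 is 36% with 48 randomised, against 58% with 50. The shift in detectable difference depends on an alpha, power and test that the article does not state, and is small on the assumptions used here. The case for correcting it is that a printed number does not follow from its printed premise. The slip does not threaten the design, the analysis or the conclusions.

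**What to change.** Keep 48 and restate the sentence in section 2.3 in one of two ways:
- 48 will be randomised, and at 20% dropout about 38 (19 per group) are expected to complete; or
- 48 allows for 16.7% dropout from a target of 40.

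Either costs one sentence and makes the stated position slightly less favourable. Recruitment, section 2.5 and the abstract stay as they are.

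For reference, the figure that keeps 20 per group at 20% dropout is 50 (25 per group). Adopting it would mean two more participants, from the 150 potential participants estimated in section 2.4, and changing 48 and 24 wherever they appear. Since 40 itself has no power basis, the size of the shortfall does not require this.

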### 2.4. Study Sample

Children and adolescents aged from 6 to 17 years old and diagnosed with CP will be recruited across schools in Madrid and Guadalajara, Spain. The estimated population for potential participants in this RCT is 150 people, who will be identified through their school Physiotherapists.

Inclusion criteria: children and adolescents with CP, aged between 6 and 17 years old; levels I-III of Gross Motor Function Classification (GMFCS) [37]; Manual Abilities Classification System (MACS) [38]; and Communication Function Classification System (CFCS) [39].Exclusion criteria: children and adolescents who have received a botulinum toxin injection in their lower limbs 6 weeks before this study or during the intervention; have undergone surgery on lower limbs in the 6 months prior to their participation in this study or during this study; or who present inability to follow the planned program due to moving to another city or another reason.

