### 2.7. Outcome Variables

After randomization, sociodemographic, clinical, and outcome variables will be collected at baseline assessment (A_0_). PT interventions will be carried out in each group for 6 weeks. After group interventions, an intermediate assessment (A_1_) will be performed, and a follow-up assessment (A_2_) will be carried out 12 weeks from baseline (Table 1). The assessments will be carried out by 2 Pediatric Physiotherapists (PPT), members of the research team, after training and consensus meetings.

Primary outcomes are as follows:

Participation: measured with the Spanish version of the Children’s Assessment of Participation and Enjoyment—CAPE, which has good internal consistency, construct validity, convergent and discriminant [40]. This instrument measures participation in extracurricular leisure activities in children and adolescents with and without disabilities during the last 4 months. It includes 55 activities, and each activity is categorized by domains (Formal, Informal) and type (Recreational, Physical, Social, Skills-based and Self-Improvement). In addition, it also measures the diversity and intensity of participation, with whom they participate and where, and the enjoyment in performing the activity.

Gross motor function: measured with the Spanish version of Gross Motor Function Measure—GMFM-SP [41], which consists of 88 items to assess the gross motor function in 5 dimensions: lying and rolling (A), sitting (B), crawling and kneeling (C), standing (D) and walking, running and jumping (E). From each dimension, a score of 0 to 100% is obtained, where a greater percentage means a greater number of items achieved. For this study, dimensions D and E are established as the goal dimensions. The minimum clinically important difference in children and adolescents with levels II and III in GMFCS is 1.5% and 1.2%, respectively [42].

Secondary variables are as follows:

Gait speed: measured with the 10 m walk test—10 MWT [43] in meters/second, which allows quick and easy assessing of walking speed. It is a commonly used test, both in clinical settings and in research, and it is outstanding for a high degree of intra- and inter-observer reliability [44].

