### 2.9. Statistical Analysis

First, a descriptive analysis of the study variables will be performed and, in the case of quantitative variables, the normality criteria will be checked. We will test whether there were differences after randomization between the two intervention groups. For this purpose, the appropriate bivariate tests will be used according to the type of variable. In a second stage, the effectiveness of the intervention will be analyzed, both in the short and medium term, adjusting for those variables that, according to previous analyses or due to the researchers’ consideration, could cause confusion. For these purposes, various logistic or linear regression models will be used (depending on the outcome variable). Finally, repeated measures models will be proposed in order to assess the evolution over time of the outcome variables.

The analysis will be performed both by protocol and by intention to treat.

The statistical package Statistical Package for the Social Sciences software (version 29, SPSS Inc., Chicago, IL, USA) or the statistical package STATA MP v18 (StataCop LLC, College Station, TX, USA) will be used.

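### Exclusion criteria that reach past randomisation conflict with the planned intention-to-treat analysis

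*Protocol article*

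**What the plan says.** Section 2.4 of the protocol article gives three exclusion criteria in one sentence.

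- The first concerns botulinum toxin and is worded "have received a botulinum toxin injection in their lower limbs 6 weeks before this study or during the intervention". Its window therefore has a part on each side of entry.
- The second concerns operations and is worded "have undergone surgery on lower limbs in the 6 months prior to their participation in this study or during this study". Here too the window runs on beyond entry.
- The third is open-ended: "or who present inability to follow the planned program due to moving to another city or another reason". It gives no time point.

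Two other sections fix the order of events. Section 2.2 says that "all participants will give their assent upon entering the trial, before matching and randomization". Section 2.7 says: "After randomization, sociodemographic, clinical, and outcome variables will be collected at baseline assessment". The six weeks of intervention follow, then the intermediate assessment A1, then the follow-up assessment A2 at 12 weeks from baseline.

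On the analysis, section 2.9 says: "The analysis will be performed both by protocol and by intention to treat".

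**The concern.** An exclusion criterion decides who may enter a trial, so it has to be answerable at entry. The second half of each of the first two criteria is not: it names an event in the treatment or follow-up period. A child who meets it has already been allocated. The ordinary effect of meeting an exclusion criterion is to leave the study, whereas intention to treat keeps every randomised child in the assigned group whatever happens later. The two sections therefore pull in opposite directions.

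At stake is the protection that randomisation gives. If children leave the comparison for things that happen after allocation, and this occurs more often in one arm or in children with a different prognosis, the groups being compared are no longer those that were randomised. There is also a practical loss. If such children are treated as ineligible and not assessed at A1 and A2, no later analysis plan can recover their data.

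**Working it through.** **1. When each criterion can be met.** The sequence from sections 2.2 and 2.7 is: consent and assent, randomisation, baseline (A0), six weeks of intervention, A1, A2 at 12 weeks.

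| Criterion (section 2.4) | Part known before randomisation | Part that falls after it |
|---|---|---|
| Botulinum toxin | injection in the 6 weeks before the study | injection in the intervention period |
| Lower-limb surgery | surgery in the 6 months before participation | surgery in the course of the study |
| Inability to follow the programme | unavailability foreseen at screening | not stated; nothing rules it out |

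The first two criteria clearly reach past randomisation. The third gives no time point and an open-ended reason, so it allows either reading.

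**2. Set against section 2.9.** Intention to treat analyses all randomised children as assigned. Section 2.4, applied literally, takes some of them out. No sentence says that a child who meets a criterion after allocation is still assessed or stays in the intention-to-treat set.

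**3. The plan's own attrition figure.** Section 2.3 starts from 40 children, allows 20% dropout and arrives at 48. This reproduces as 40 × 1.20 = 48. (Dividing instead, 40 / 0.80 = 50, and 48 × 0.80 = 38.4 would remain.) The present point does not depend on this figure, which is an overall allowance with equal numbers in each arm. It only gives a scale: 0.20 × 24 = 4.8, about five children per arm.

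**4. What removal could do to the comparison.** Let p be the proportion removed from an arm and Δ the mean of those kept minus the mean of those removed, in SD units. The full-arm mean is (1 − p) × kept + p × removed, so removal raises the arm's mean by p × Δ. The bias in the between-group difference is

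p(EG) × Δ(EG) − p(CG) × Δ(CG).

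- Equal removals, unrelated to allocation: the two terms cancel and the bias is about zero.
- Illustration, all assumed: p(EG) = 0.20, p(CG) = 0, Δ from 0.5 to 1.0. Bias = 0.20 × 0.5 = 0.10 to 0.20 × 1.0 = 0.20 SD.
- Second illustration, also assumed: no true effect, normal outcome, removal in one arm only of the fraction d lowest on a trait correlated ρ with the outcome. Bias = ρ × φ(c) / (1 − d), where φ is the standard normal density and c is the d-quantile of the standard normal distribution.

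| ρ | d = 5% | d = 10% | d = 20% |
|---|---|---|---|
| 0.3 | 0.03 | 0.06 | 0.11 |
| 0.5 | 0.05 | 0.10 | 0.18 |
| 1.0 | 0.11 | 0.20 | 0.35 |

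The range runs from about zero to 0.35 SD, and the sign reverses if the control group loses more such children. The document gives none of p by arm, Δ or ρ.

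**5. Whether imbalance is plausible.** For non-attendance it is. Section 2.8.1 gives the experimental group two face-to-face sessions a week for six weeks (2 × 6 = 12), each of about 75 minutes, at the university unit. Section 2.8.2 keeps controls on their regular physiotherapy. For injection and surgery, nothing in the document suggests a difference between arms.

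**The case against.** The best defence is that section 2.9 plans two analyses, and two analyses imply two different sets. On that reading the later events define who leaves the per-protocol set, while intention to treat keeps everyone. This is coherent, and no sentence states that such children leave the intention-to-treat set. What it does not remove is that section 2.4 lists the events as exclusion criteria, not as protocol deviations. The benign reading has to be supplied by the reader.

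Four stronger readings are tempting, and the document does not support them.

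- A reader might infer that the intention-to-treat set is in fact a completers set. That rests on taking the third criterion to mean non-adherence. It speaks of inability, has no time marker, and can naturally mean unavailability known at screening.
- A reader might infer a bias towards the experimental treatment. That needs removals concentrated in that arm and a worse prognosis in those removed; neither is stated. The burden is also partly shared: controls take the same education programme (six online sessions of about 60 minutes), and the practical barriers to telecare named in section 3 apply to both arms.
- A reader might object that neither analysis is named as primary. A statistical analysis plan commonly settles that, and none is shown here, so it is not held against the protocol.
- A reader might see an error in the injection criterion covering the intervention while the surgery criterion covers the study. Nothing requires two different procedures to share a window.

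**Conclusion.** The concern holds in a limited form. Two exclusion criteria name events after randomisation, and a third is open enough to be applied in that way. Taken literally, they remove randomised children and conflict with the intention-to-treat commitment. This is a fault in a rule that the protocol states, not a detail left to another document.

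No size or direction of bias can be derived. The figures of 0.03 to 0.35 SD are illustrations that assume removal from one arm only and a link between removal and outcome. The conflict between sections 2.4 and 2.9 rests only on the stated order of events and the usual meanings of exclusion and intention to treat.

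**What to change.** Reconcile sections 2.4 and 2.9 as follows.

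1. In section 2.4, limit the exclusion criteria to facts known before randomisation: injection or surgery before entry, and unavailability that can be foreseen at screening.
2. State that injection, surgery, relocation or non-attendance after randomisation is recorded; that the child is still assessed at A1 and A2 where possible; and that the child is analysed in the assigned group under intention to treat.
3. State that these later events serve only to define the per-protocol set.

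This concerns eligibility wording, follow-up and analysis sets. It takes no position on the clinical handling of a child who has an injection or surgery.

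The cost is a wording change and some effort to assess children who stop attending. The estimate may become slightly less favourable. The change is best made before the A1 assessments, because outcomes not collected then cannot be recovered.
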